Above- or below-average resources are recorded with the median of differences (pretest-posttest estimates of resources), leading to other hypotheses: (1) above-average resources are associated with lower workload, and below-average resources are associated with higher workload (hypothesis 2); (2) above-average resources are associated with higher work engagement (hypothesis 3a); (3) when resources increase, work engagement increases (hypothesis 3b); (4) if resources increase (exclusion of technical competence as a resource), then readiness for technology increases while the burden decreases (hypothesis 4a); (5) as technical competence (resource) increases, the burden decreases (hypothesis 5a); (6) when technical competence (resource) decreases, the burden increases (hypothesis 5b); and (7) above-average work engagement leads to higher readiness for technology, and below-average work engagement leads to lower readiness.

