#### Work-Related Evaluation

Physicians and nurses who are or will be involved with the project take part in the work-related evaluation. With medium to small effect sizes (η^2^>0.05 and <0.15), a type-1 error (α) of 5%, and a type-2 error (β) of 20% (80% power), a minimum number of 120 people per measurement point is required for the work- and project-related evaluation (60 people each in the control and treatment groups). A total of 4 employees per clinic at measurement time t0 and 4 employees at measurement time t1 are included in the sample. This results in 31 × 8 = 248 elevations. Care is taken to interview physicians and nurses in equal parts, all of whom are or will be involved in the project measures.

Regarding the interviews for the assessment of the objectives and project implementation, 2 persons from the nursing service and 2 persons from the medical profession are to be interviewed at time t1 in the clinics that are already implementing the new form of care. Approximately 72 people from at least 18 clinics will take part in the interviews.

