Work resources are measured using the German-language questionnaire on resources and requirements in the world of work [54]. For the EXPERT project, 11 items are used, which relate to the resources “Leadership Support,” “Feedback,” “Peer-Support,” “Transparency,” “Diversity,” “Meaningfulness,” “Role Clarity,” “Learning Opportunity,” “Knowledge Management,” “Team Atmosphere,” and “Qualification.” All items are formulated as statements (eg, “I will be informed about all important content when implementing the new measures” [“transparency” resource]), which are rated on a scale from 1 to 6 (1=*not at all true*; 6=*completely true*).

Affinity for technology is measured using the German-language short scale for measuring readiness for technology [55]. It is a questionnaire with 12 items in the 3 scales “TB acceptance,” “TB control belief,” and “TB competence,” of which 9 items are used in this study. The item formulations have been adapted to the EXPERT project (eg, “I am very interested in the new telemedicine application” [acceptance scale], “It essentially depends on me whether I am successful in using the new telemedicine application” [control conviction scale], and “For me, dealing with technical innovations is usually too much to handle” [competence scale]).

The software ergonomics of the new telemedicine application are assessed using the German-language questionnaire Norm of the International Standard Organization 9241/10 [56,57]. On the basis of this instrument, software is evaluated regarding “adaptivity to requirements,” “comprehensibility,” “task appropriateness,” “ability to describe itself,” “fault tolerance,” “individualizable,” and “learning conduciveness.” The assessment of the 7 items is made on a bipolar scale based on symbols (from “– – –” to “+++”).

Finally, employees provide information about their profession (physician or nurse), whether they hold a management position (yes or no), and whether they already had experience in the use of telemedicine before the EXPERT project (yes or no).

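### Three work-related hypotheses reduce graded scores to above or below average, which loses information, and the resource cut needs individual pre-post differences that anonymous questionnaires cannot supply

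*Protocol article*

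**What the plan says.** The protocol article, under Work-Related Hypotheses, fixes the classification: "Above- or below-average resources are recorded with the median of differences", the differences being between pretest and posttest resource estimates. It is used in hypothesis 2, "above-average resources are associated with lower workload, and below-average resources are associated with higher workload (hypothesis 2"), and in hypothesis 3a, "above-average resources are associated with higher work engagement (hypothesis 3a"). The last hypothesis in the list is worded in the same way for another score: "above-average work engagement leads to higher readiness for technology, and below-average work engagement leads to lower readiness". No cut is given for engagement.

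Not every work-related hypothesis is a split. Hypothesis 3b concerns the same two constructs as 3a but reads "when resources increase, work engagement increases (hypothesis 3b"). Hypotheses 4a, 5a and 5b are likewise worded as increases or decreases.

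Under Outcomes and Measures, Questionnaires, resources are 11 items each rated 1 to 6, and work engagement is 3 items each rated 0 to 6.

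Under Data Sampling, Work-Related Evaluation, "a minimum number of 120 people per measurement point is required for the work- and project-related evaluation", made up of 60 control and 60 treatment respondents, at alpha 5%, 80% power and eta-squared between 0.05 and 0.15. With 4 staff per clinic at each of two time points, 31 clinics give 248 questionnaires.

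Under Data Analysis, Work-Related Evaluation, completed questionnaires are stored anonymously. Because of staff turnover, repeated-measures analysis is excluded. The inferential analysis described is a time-by-group analysis of variance.

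**The concern.** The three hypotheses claim graded relations: more resources go with less workload and more engagement, and more engagement goes with more readiness for technology. A two-way split is not needed to test any of them, and the article gives no threshold that would justify one.

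For resources, the median makes the label relative to whoever answers. About half the sample is called above average whatever the scores are. If resources rise in the intervention phase, as hypothesis 1b predicts, a respondent whose resources rose by less than the median is classed as having below-average resources.

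Two things are at stake. First, information is thrown away, so a real association is more easily missed. Second, the cut is defined on a quantity that the survey cannot produce for a respondent.

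**Working it through.** **Inputs from the article.** Alpha 5%; eta-squared 0.05 to 0.15; 120 responses per measurement point; 248 in total.

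**The plan's own figure.** For a test with 1 numerator degree of freedom and noncentrality λ = n·η²/(1−η²), 80% power needs a total of 152 at η² = 0.05, 120 at 0.0625, 73 at 0.10 and 47 at 0.15. The stated 120 lies inside this span. It is matched at about 0.0625, but that value is solved backwards from 120 and stands nowhere in the article. The figure is therefore neither confirmed nor shown to be wrong. It belongs to the comparison of treatment with control, where nothing is split.

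**Information lost by a median split.** For a normal score with a linear relation, the split keeps 2/π = 0.637 of the explained variance, a loss of 1 − 0.637 = 36%. Other assumed shapes gave these losses: uniform 25%, a simulated 3-item 0-to-6 scale 35%, double-exponential 50%, exponential 52%.

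**Illustrative power.** The split replaces η² by 0.637·η². For example, with n = 120 and η² = 0.05:
- full scale: λ = 120 × 0.05/0.95 = 6.32, power 70%
- split: η² = 0.0318, λ = 120 × 0.0318/0.9682 = 3.94, power 50%

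| n | η² | Full scale | Median split |
|---|---|---|---|
| 120 | 0.05 | 70% | 50% |
| 120 | 0.0625 | 80% | 60% |
| 120 | 0.10 | 95% | 81% |
| 120 | 0.15 | 99.5% | 94% |
| 248 | 0.05 | 95% | 81% |
| 248 | 0.10 | 99.9% | 98% |

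Assumptions: normal score, linear relation, independent responses, no clinic effect, two-sided test. These rows use the score from a single questionnaire, not a pre-post difference.

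**Can the resource cut be formed?** Side by side:
- Work-Related Hypotheses classifies resources by the median of pretest-posttest differences.
- Data Analysis stores questionnaires anonymously, expects different staff at the two time points and excludes a repeated-measures design.

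A respondent-level difference needs two linked answers from one person, and none are linked. At most, differences of clinic means could be formed, if the clinic is recorded. With 31 clinics (an assumption), power over η² 0.05 to 0.15 would be about 24% to 62% on the full scale and 16% to 42% after a split.

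**The case against.** A reader might infer that the split cuts tests planned at 80% power to about 60%. The article does not support this. Its 80% is for 60 control against 60 treatment respondents, and no power, sample size or test is stated for hypotheses 2, 3a or the engagement-readiness hypothesis. The fall from 80% to 60% appears only at a back-solved effect size with one measurement point. With all 248 questionnaires, the split test keeps about 81% power or more across the stated effect range, under the assumptions above. This objection stands, so the power figures are illustrations.

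A reader might also infer that all work-related hypotheses are split, or that engagement is cut at its median. Neither follows. Only three hypotheses use the above- or below-average wording, and the median is named for resources alone. The article says comparative values exist for its instruments, so average engagement could be meant relative to those. The remarks about a sample-specific cut therefore apply to resources only. For engagement, the defect is a two-way wording with an unstated cut.

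Finally, these are secondary hypotheses in a staff survey, and test details are often left to an analysis plan. That limits the weight of the point but does not remove it: the article itself states the classification for resources, and that definition conflicts with its own data collection.

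**Conclusion.** The point holds in this limited form. Hypotheses 2 and 3a rest on a median split of a graded score, and the engagement-readiness hypothesis on a two-way classification with no stated cut. A median split loses about 36% of the information for a roughly normal score and a linear relation, and about 25% to 50% for other shapes tried. In illustrative power, that is about 20 percentage points at the bottom of the stated effect range with 120 responses, and about 14 points at η² 0.10 with 120 or at η² 0.05 with 248. At the top of the range it is small. Clinic clustering is ignored throughout.

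Separately from the loss of information, the resource cut cannot be formed per respondent as described, so the hypotheses section and the data analysis section must be reconciled. The change should be made, but it does not touch the primary complication outcome or the trial's main conclusion.

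**What to change.** Restate hypotheses 2 and 3a and the engagement-readiness hypothesis as associations with the continuous resource or engagement score, and drop the classification by median of differences. For each, regress the outcome scale (workload, work engagement or readiness for technology) on the respondent's score from the same questionnaire, with measurement time and group as factors and allowance for clinic. Report the slope with its 95% confidence interval. State plainly that this tests score level, not individual change. Any median-split table should be description only.

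Before fixing the model, confirm that the clinic is recorded with each response. The article describes questionnaire links by group, cohort and time point, and does not list clinic among the background items.

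The cost is wording of the hypotheses and of the work-related analysis. No further items or respondents are needed, provided that the clinic is already recorded. There are two downsides: a slope is slightly less simple to present than two group means, and hypotheses 2 and 3a move from change to level.

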**Figure 1 figure1:**
[figure not shown]
Overview of work-related hypotheses concerning the relationship among work resources, workload, work engagement, and readiness for technology.

## Methods

### Study Design

#### Clinical and Health Economic Evaluation

For the organization and evaluation of the new form of care, a stepped-wedge design was chosen [36,37]. In a stepped-wedge design, there are different clusters that start recruitment at the same time in the control phase. The individual clusters then move gradually into the intervention phase in randomized cohorts. In the EXPERT project, there is a transition phase between the control and intervention periods, which serves to implement and test the new form of care in the individual clinics as well as train the staff.

Randomization in the EXPERT project will take place at the hospital level. There are 31 hospitals participating in the study. Each clinic forms a cluster that belongs to 1 of 4 cohorts. The clusters within a cohort always enter the next study phase (transition or intervention phase) at the same time. The study will be conducted over a period of 24 months (18-month recruitment period+6-month follow-up of the last enrolled person). Data collection regarding the individual course of treatment takes place from the time of enrollment in the patient sample until 6 months later. Figure 2 shows the planned course of the study in the stepped-wedge design.

**Figure 2 figure2:**
[figure not shown]
Representation of the stepped-wedge design in the EXPERT (Extremity Boards for process optimization, evaluation, risk minimization, and therapy optimization for fractures with soft tissue damage or postoperative infection of the lower extremities in the trauma network) project.

#### Work-Related Evaluation

For the ergonomic evaluation, the “difference-in-difference” method will be used within the stepped-wedge design [38]. This methodological approach includes a treatment group and a control group, each of which is examined at 2 measurement points (t0 and t1). In the treatment group, but not in the control group, an intervention takes place between the measurement points. The first difference that is measured refers to a possible change from measurement time t0 to measurement time t1. This is calculated for both the treatment and control groups. The second difference is the difference between these 2 differences (ie, the difference within the control group is subtracted from the difference within the treatment group). The result can be interpreted as a causal effect of an intervention [38,39].

In the EXPERT project, the clinics that have not yet implemented the project measures serve as a control group, which will be evaluated at the same time as the clinics that are already implementing the new measures. Cohorts 1 and 2 are the treatment group, whereas cohorts 3 and 4 act as the control group.

### Data Sampling

#### Clinical and Health Economic Evaluation

Studies show that, in approximately 40% of cases, complications occur during the treatment in open fractures [40]. The new form of care is realistically intended to reduce the complication rate to 30%. A type-1 error (α) of 5%, a type-2 error (β) of 20% (80% power), and an intraclass correlation coefficient of ρ=0.05 are assumed [36]. Considering the transition phase and a dropout rate of 20%, the total number of cases required to demonstrate a treatment effect is 3366 patients (of whom n=1377, 40.91% would be in the control phase; n=1428, 42.42% would be in the intervention phase; and n=561, 16.67% would be in the transition phase). This equates to 17 patients per hospital per 3-month interval.

Only patients who can give consent and who have statutory health insurance will be included in the project and will give their written consent to participate and share their data in the use of telemedicine. The study will include patients with fractures of the extremities with open soft tissue damage (according to Gustilo et al [41]) or with postoperative complications (according to the criteria of the Association of the Study of Internal Fixation Anti-Infection Task Force) or people with unplanned resurgery within 6 months of initial surgery. Specifically, these are *International Statistical Classification of Diseases and Related Health Problems, 10th Revision* (*ICD-10*), diagnoses [42] related to open soft tissue damage in fractures or dislocations, amputations of the lower extremity, infections of joints or joint endoprostheses of the lower extremities [43], and pseudarthrosis and delayed fracture healing of the lower extremity (see the list in Textbox 1).

Patients who are not capable of giving consent, who do not give their consent to participate or to data transfer, or who do not have statutory health insurance will be excluded from the study. Also excluded will be persons to whom the aforementioned *ICD-10* diagnoses do not apply (ie, who do not have a fracture of the extremities or extremities or have a closed fracture of the extremities without open soft tissue damage and who do not experience a postoperative complication within 6 months of initial surgery). The inclusion and exclusion criteria are summarized in Textbox 2.

*International Statistical Classification of Diseases and Related Health Problems, 10th Revision* (*ICD-10*), diagnoses to be included in the EXPERT (Extremity boards for process optimization, evaluation, risk minimization, and therapy optimization for fractures with soft tissue damage or postoperative infection of the lower extremities in the trauma network) study.

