**Methods:**

Using a digital platform, physicians from 31 hospitals present patient cases to an interdisciplinary group of experts from the fields of plastic surgery, infectiology, hygiene, and others. The group of experts from the environment of the University Hospital Münster promptly makes a joint treatment recommendation for the individual case. The plan is to examine 3300 patients with open fractures or surgical complications. As consortium partners, there are also 3 statutory health insurance companies. The extent to which the therapy recommendations are effective and contribute to cost reduction in the health care system will be empirically investigated in a stepped-wedge cluster-randomized design. In addition, medical and nonmedical professional groups involved in the project will be asked about their work in the project (in total, 248 clinic employees). The primary outcome is the complication rate of open fractures or the occurrence of postoperative complications. As secondary outcomes, the number of antibiotics administered, limb function, and quality of life will be assessed. The health economic evaluation refers to the costs of health services and absenteeism. For the work-related evaluation, workload, work engagement, work-related resources, readiness for technology, and ergonomic aspects of the new telemedical technology will be collected. In addition, clinic employees will give their assessments of the success of the project in a structured telephone interview based on scaled and open-ended questions.

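### The 3366-patient target implies 33 hospitals, not the stated 31, and with one transition interval per hospital the stated 80% power is about 57–62% under a period-adjusted two-sided analysis

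*Protocol article*

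**What the plan says.** Under Methods, Data Sampling (Clinical and Health Economic Evaluation), the article takes a control rate from studies in which "in approximately 40% of cases, complications occur during the treatment in open fractures" and aims for 30% under the new form of care. It adds: "A type-1 error (α) of 5%, a type-2 error (β) of 20% (80% power), and an intraclass correlation coefficient of ρ=0.05 are assumed". The result, said to allow for the transition phase and a dropout rate of 20%, is then given: "the total number of cases required to demonstrate a treatment effect is 3366 patients". The total is split into 1377 control, 1428 intervention and 561 transition patients, followed by "This equates to 17 patients per hospital per 3-month interval".

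Under Methods, Study Design (Clinical and Health Economic Evaluation), "There are 31 hospitals participating in the study". They are allocated to 4 cohorts, recruitment lasts 18 months, and a transition phase lies between the control and intervention periods. The abstract says: "The plan is to examine 3300 patients with open fractures or surgical complications".

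Under Data Analysis, outcomes are to be modelled by regression that takes account of temporal effects. The limitations section gives the handling of time effects as a reason for choosing the design.

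**The concern.** There are two separate problems.

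- **Counts.** The total, its three-way split and the rate per hospital agree with one another, but only for a number of hospitals that the article does not have.
- **Power.** In a stepped wedge analysed with period effects, most of the information comes from calendar intervals in which some hospitals are in control and others in intervention. A transition interval in every hospital removes cells at the changeover, where they are most informative. Adding patients to fill the gap does not replace that lost contrast.

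If the power is overstated, readers are told that a true 10-point reduction would be missed 20% of the time when the figure may be about 40%. A non-significant result would then be over-read as evidence of no benefit.

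**Working it through.** **1. Reproduce the stated total.** Inputs from the article: 17 per hospital per interval; 18 months ÷ 3 = 6 intervals; total 3366.

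- 3366 ÷ 17 = 198 hospital-intervals = 33 × 6.
- 561 ÷ 17 = 33, so each of 33 hospitals has one transition interval.
- 1377 ÷ 17 = 81 and 1428 ÷ 17 = 84. Cohorts of 9, 8, 8 and 8 hospitals with 1, 2, 3 and 4 control intervals give 9 + 16 + 24 + 32 = 81 control and 36 + 24 + 16 + 8 = 84 intervention hospital-intervals.

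Every figure reproduces with 33 hospitals. With 31, the total is 31 × 6 × 17 = 3162, of which 31 × 17 = 527 are in transition. Control and intervention then each hold 1292 to 1343, depending on which cohort has 7 hospitals. Spreading 3366 over 31 hospitals needs 3366 ÷ 186 = 18.1 per interval.

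**2. Layout implied by the counts** (C control, T transition, I intervention):

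| Cohort | 1 | 2 | 3 | 4 | 5 | 6 |
|---|---|---|---|---|---|---|
| 1 | C | T | I | I | I | I |
| 2 | C | C | T | I | I | I |
| 3 | C | C | C | T | I | I |
| 4 | C | C | C | C | T | I |

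Cohort 1 starting the new care in project month 7 (Data Analysis, work-related part) fits this. Control and intervention hospitals coexist only in intervals 3 and 4.

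**3. Power.** The model is Hussey–Hughes: hospital random intercept, categorical period effects, generalised least squares on cell means.

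- Evaluable per cell: 17 × 0.8 = 13.6.
- Total variance: 0.35 × 0.65 = 0.2275. Between hospitals: 0.05 × 0.2275 = 0.0114. Within a cell: 0.95 × 0.2275 ÷ 13.6 = 0.0159.
- Power = Φ(0.10 ÷ SE − 1.96).

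| Design | SE | Power |
|---|---|---|
| 31 hospitals, transition excluded | 0.0465 | 57% (0.10 ÷ 0.0465 = 2.15) |
| 31 hospitals, transition kept with own indicator | 0.0440 | 62% |
| 33 hospitals, transition excluded | 0.0443 | 62% |
| 31 hospitals, five intervals, no gap | 0.0347 | 82% |
| 33 hospitals, five intervals, no gap | 0.0334 | 85% |

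The 31-hospital rows put 7 hospitals in cohort 1 or 4. If the short cohort is 2 or 3, the SE with transition excluded is 0.0457 and power is about 59%.

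**4. Other assumptions.**

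- 31 hospitals, transition excluded, linear time: about 62%.
- Transition excluded, ICC 0 to 0.10: 57–69% (31 hospitals) or 62–73% (33).
- All 3366 recruited in 31 hospitals (18.1 × 0.8 = 14.5 evaluable), transition excluded: about 60%.
- Difference detectable with 80% power, 31 hospitals, transition excluded: 2.80 × 0.0465 = 0.130, about 13 points.

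**5. Where the stated figure may come from.** The article prints no formula. One no-gap reconstruction comes close. Starting from N = 708 for two proportions, the stepped-wedge design effect with 4 steps, 2 baseline intervals, 17 per cell and ICC 0.05 is (6.05 ÷ 4.35) × 0.38 = 0.5285. Then 708 × 0.5285 × 6 = 2245; ÷ 0.8 = 2806; × 6/5 = 3368. Another version (1 baseline interval, N = 712) gives 13 evaluable per cell for 31 hospitals, and 13 ÷ 0.8 = 16.25, rounded up to 17. For 33 hospitals, however, it gives 12, hence 15. The two recipes are not compatible, so the method actually used cannot be identified.

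**The case against.** The strongest reply is that the article says the transition phase was considered, cites a method reference that is not at hand, and never says that transition patients leave the primary model. It even counts them in the number required. Their handling is a detail commonly left to the full protocol or analysis plan. If they were grouped with a neighbouring phase, and that grouping carried the full 10-point contrast, power in 31 hospitals would be about 84%. Sidedness is not stated either: a one-sided 5% test with transition excluded gives about 69% for 31 hospitals. The abstract's 3300 may simply be 3366 rounded.

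Much of this stands as a limit on the claim. The 57% is conditional, and the conditions must be given with it. It does not rescue the 80%. The transition phase serves to implement and test the new care and to train staff, so assuming a full effect there (or none, if grouped with control) is optimistic. One-sided testing with transition excluded reaches about 80% only with 33 hospitals and no dropout, against the stated 20% dropout.

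A reader might infer that the authors ignored the gap and added the transition patients only as extra headcount. That is plausible, since a no-gap formula returns 3368, but it is not shown: the formula is not printed, and two incompatible recipes fit parts of the result. A reader might also infer that 3162 is the correct total. The documents do not settle this, because 3366 is given as the number required and the rate or the hospital count could be the outdated figure.

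**Conclusion.** The count mismatch is certain and needs no model: the total, the split and the rate describe 33 hospitals, and the article has 31. The abstract's figure is a minor third value.

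The stated 80% power is not delivered by the described design under a period-adjusted, two-sided 5% analysis at ICC 0.05 with 20% dropout. In 31 hospitals it is about 57% with transition patients excluded, and about 62% with a transition indicator or linear time. In 33 hospitals with exclusion it is about 62%. Most of the shortfall comes from the gap; the two missing hospitals cost about 4 points.

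This rests on one 3-month transition interval per hospital (from 561 = 33 × 17, as Figure 2 is not shown), near-equal cohorts, ICC on the proportion scale, a constant treatment effect and a normal approximation. The indicator analysis depends more on the ICC than the exclusion analysis: at an ICC of exactly zero it would reach about 80%, but the plan assumes 0.05.

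**What to change.** 1. Reconcile the hospital count, the per-interval rate and the total across the abstract, Study Design and Data Sampling. If 31 hospitals and 17 per interval stand, the total is 3162 with 527 in transition. If 3366 stands with 31 hospitals, the rate is about 18 per interval and power is about 60% with transition patients excluded. The authors must say which holds.
2. Restate the power for 40% versus 30% with the transition gap included (about 57–62%), or give the detectable difference (about 13 points at 80% power with transition patients excluded). State the formula, the sidedness and the handling of transition patients.
3. Keep transition patients in the primary model with a separate transition indicator. The SE falls from 0.0465 to 0.0440, a gain of about 5 points of power, which does not restore 80% at the stated ICC.

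The cost is a text correction and one model term, with no extra patients. The stated power becomes less favourable.
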